### Study intervention

#### Theoretical basis of the intervention

Social Cognitive Theory [35] and models of persuasive communication for attitude and behavioral change [36] were used to structure the program to meet the intervention objectives. Bandura's Social Cognitive Theory (1986) has been broadly applied in public health intervention, and it has been used here to identify the critical elements of child socialization regarding cigarette smoking. Specifically, these elements include a) perception, where a child perceives the expressed thoughts and actions of parents or other socializing agents, b) cognitive rehearsal, where a child recalls and assigns meaning to what has been perceived, c) behavioral rehearsal, where a child communicates or acts in a manner consistent with what has been learned and receives feedback regarding those thoughts and behaviors, and d) motivation, where a child experiences positive (or negative) reinforcements for specific communications or actions. Each element of the program was designed to address one or more of these child socialization processes.

Communication models, particularly the Elaboration Likelihood Model [36], offer substantive input as regards the design of persuasive communications. Of particular importance is that participants vary with respect to the perceived relevance and salience of health communications, and the intervention design should take this variability into account. For example, we expect some parents to engage in argument-based processing of program content (where message content most affects parental response to program recommendations), and others to engage in cue-based processing (where peripheral cues such as print design most affect parental response to program recommendations). The program information has been structured to address both modes of information processing.

#### Intervention Condition

Parents and children in the intervention condition will receive five printed activity modules by mail at four-week intervals. The aim of the modules is to achieve progressive development of parent-child socialization activities. Activities have been designed to gradually increase parental skills and comfort level in communicating with children about smoking, addiction, and expectations regarding abstinence. Each activity module includes a high concentration of structured interactions that engages parent and child simultaneously, such as games, scripted role-plays, contests, and interviews. These structured interactions are a key technique for facilitating parent-child engagement in the intervention [37].

Each module aims to modify different socialization variables, module 1 targets general communication about smoking and makes parents and child comfortable with communicating about smoking, module 2 concentrates on influence of smoking messages (i.e., influence of media, sport events, and people around us), module 3 focuses on setting rules about smoking to protect their child from experimentation with tobacco. Module 4 is an extension of module 3 and involves creating a smoke-free house and -environment to keep the child away from second hand smoking. The last module, number 5, increases children's awareness regarding the influence of smoking classmates and friends and increases their ability to handle peer pressure. All five modules contain a communication sheet for parents. These sheets provide additional background information about the subjects discussed in the modules and communication tips for parents. Finally, a booster module will be delivered 12-months post-baseline.

#### Newsletters

Between the activity modules, parents will receive a series of digital newsletters in their email box. These newsletters will be sent after modules two, three, and five. The newsletters aim to maintain commitment to the program. The newsletters will inform parents about the background of Smoke-free Kids, review the activity modules that parents and child receive in the mail, and announce the winners of different program contests (e.g., 'drawing an anti-smoke message,' 'compose the longest sentence with magnet stickers,' and 'writing a story including an anti-smoking message').

#### Booster module

Evaluations of smoking prevention programs for adolescents indicate that repeated exposure to the key elements of the intervention program can strengthen program effects. A booster module will be developed with the theme 'Staying smoke-free.' This module includes a self-assessment component; i.e., parents and children will evaluate which anti-smoking skills they have practiced well, and which ones they could improve. Additionally, motivational information to stay smoke free throughout the high school years will be provided.

#### Control condition

For the families in the control condition, a fact-based program has been developed. An alternative program will be provided for controls because we assume it is unethical to recruit them for an intervention program while not offering them a program afterwards. Providing alternative materials for controls also helps maintain comparable response rates when follow-up data are collected from the two arms of the study. The factsheets provide information on youth smoking and focuses parents' attention on macro-level variables relevant to youth smoking, but not targeted by the intervention version of the program (for example, smoking prevalence among youths, ingredients of cigarettes, tobacco legislation). The criterion for selecting factsheets information was that the same information would be available in local, state, or national print or broadcast media. Although the information provided could increase control condition parents' knowledge regarding tobacco issues, this awareness is not expected to affect anti-smoking socialization processes. Moreover, it is difficult to retain parents in the study without providing them anything of a program. Both factsheets and modules will be mailed at the same time to participants in the control and intervention condition (Figure 2). Similar to the children in the intervention condition, the children in the control condition will also receive incentives (magnet stickers & Frisbees) to thank them for participating.

**Figure 2 F2:**
[figure not shown]
**Intervention program**. An overview and time frame of the intervention program.

All the U.S. materials were translated and adapted to the Dutch language. This was done in collaboration with STIVORO (Dutch Institute for Smoking Prevention), the Trimbos Institute (Netherlands Institute of Mental Health and Addiction), and professional translators. The following adaptations were made for the Dutch intervention. For instance, some assignments were not suitable for the Dutch intervention because they were too culturally specific or they concerned issues that have changed since the U.S. program started. For instance, the U.S. intervention included assignments that referred to tobacco advertising, which is prohibited nowadays. Moreover, while the original program targeted smoking mothers, the Dutch program was made accessible to both smoking and non-smoking mothers; therefore, the focus of some modules needed to be changed. Finally, the layout of the modules has been modernized and adapted (i.e., cartoons).

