### Asthma

Health effects of smoking initiation are more profound on adolescents with asthma compared to adolescents without asthma. People with asthma who smoke are more likely to develop lung diseases and COPD [23] over time compared to those who do not smoke. Worldwide, the prevalence of asthma varies across countries and age groups. The prevalence of asthma among children aged 7-9 years old ranges from 0% to 20.3% and among 13-14 year olds from 0.1% to 16% (ISAAC study: [24]). Our institute is one of the participating collaborating parties in the ISAAC study, the worldwide epidemiological project on the prevalence of asthma and asthmatic symptoms. According to Dutch data collected from 10,087 adolescents aged 12-14 years old, 13% of the participants reported lifetime asthma and 7% reported asthmatic symptoms in the last 12 months [25]. Although one might expect that- due to the long-term negative consequences of cigarette use - adolescents with asthma would be less likely to start smoking, the contrary seems to be true (see also [26,27]). The prevalence of regular smoking among adolescents with asthma is as high as among their non-asthmatic peers [28]. In addition, adolescents with asthma are more likely to have parents who smoke than adolescents without asthma [29]. Smoking parents are less involved in anti-smoking socialization than non-smoking parents [22]. Therefore, it is important to involve this vulnerable group in smoking prevention and to examine whether the effects of the Smoke-free Kids program are different for children with and without asthma.

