### Aim and hypotheses

The primary aim of the study Smoke-free Kids is to assess the effectiveness of this prevention program among children aged 9-11 years old in the Netherlands. Both short-term (after 6 months) and long-term (12, 24, 36 months) effects of the intervention will be tested. Two hypotheses will be tested. First, in line with the U.S. findings, we expect that the program will lead to lower likelihood of children's smoking initiation. Specifically, we expect that children in the intervention condition, relative to controls, will be less likely to engage in smoking at follow-up based on the findings of Smoke-free Kids in the U.S. We will test whether the effects of the intervention program are different for children with asthma. Second, we expect that the program will lead to significant increases in anti-smoking socialization of children. Specifically, we expect that parents included in the intervention program (as compared to controls) (a) will be more engaged in constructive communication on smoking topics, (b) will have more confidence in discussing smoking matters and greater self-efficacy to prevent their children from smoking, (c) will set and keep stricter household rules against smoking and establish a non-smoking contract with their children, and (e) will be more likely to monitor children's and peers' smoking-related activities.

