### Participants

#### Recruitment

Families are recruited from primary schools, media, and health professionals. Specifically, primary school boards are asked to distribute letters to all children aged 9-11 years old and to request that children give this letter to their parents. This letter includes information about the study and inquires whether parents want to be involved in our study. If parents agree to participate, they can provide their contact information by filling out a short screening self-administered questionnaire (that includes items assessing parental smoking status and possible asthmatic symptoms of the child) and return it in the enclosed envelope. It is also possible to register online via a secured webpage. To recruit children with asthmatic symptoms, several local and national newspapers, a local television station, and different health related prevention websites (e.g., Dutch Asthma Foundation, Dutch Institute for Smoking Prevention) agreed to assist in announcing the study on a population level. Furthermore, health professionals (i.e., general practitioners, pharmacist, and lung specialists) are requested to place posters with accompanying flyers in their waiting rooms.

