### Sample Size Calculation

Based on the findings from the U.S. trial, we expect a 10% difference in smoking initiation rates between the intervention and control conditions. Equal cell sizes are assumed for study cells and power of .80 was targeted. The primary hypothesis will be tested at an overall two-sided significance level of 0.05. We used the general-purpose statistical software package Stata to calculate the estimated sample sizes for two-sample comparison of proportions. Based on the U.S. data and the prevalence of smoking in 12 to 14 year olds (age of the children at 36-months follow-up), which is around 30%, we would need 428 children per condition. In these power analyses, we corrected for the fact that data are clustered (children are nested within schools) and the fact that we will apply multiple imputation in the case of missing data. Thus, 856 children (and mothers) would be included to test the effectiveness of Smoke-free Kids. A sub-goal of the study is to examine whether there is any difference between the children with and without asthma or asthmatic symptoms. To test the moderating effect of asthma or asthmatic symptoms, we will include a subsample of 200 children with asthma or asthmatic symptoms. This allows us to test whether the effect of the intervention is different for children with asthma. Eventually, the study is over-enrolled. Overall, a total of 1479 children (and mothers) will participate in the study: 1399 never smokers and 80 ever smokers. The asthmatic subsample includes approximately 239 children whose mothers reported their child to have had an asthmatic period at least once in their lives. This allows us to test whether the effect of the intervention is different for children with asthma. Moreover, having 623 additional participants allows us to do complex analyses and to test several other moderators and mediators. In accordance with the intention-to-treat philosophy, all children randomized to one of the conditions are included in analyses to test the study hypotheses.

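### The 10-point effect is taken from a programme for smoking mothers and applied to all mothers without a reason; maternal smoking, already collected, is neither a named moderator nor a stated covariate

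*Protocol article*

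**What the plan says.** **Source of the effect.** Aim and hypotheses ties hypothesis 1 to the U.S. work: "First, in line with the U.S. findings, we expect that the program will lead to lower likelihood of children's smoking initiation". Sample Size Calculation does the same for the effect size: "Based on the findings from the U.S. trial, we expect a 10% difference in smoking initiation rates between the intervention and control conditions". The inputs there are a rate of around 30% at 36 months, two-sided 0.05, power 0.80 and 428 children per condition, said to be already corrected for clustering and missing data.

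**Population.** Background describes the U.S. programme as one for parents who smoke. The adaptation text under Figure 2 says: "while the original program targeted smoking mothers, the Dutch program was made accessible to both smoking and non-smoking mothers". It adds that some modules were refocused for this reason. Eligibility Criteria contains no condition on maternal smoking.

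**Moderators.** Asthma is the only one named. Sample Size Calculation says that the over-enrolment allows the team "to test several other moderators and mediators", without listing them. Randomization stratifies by school and number of children with asthma. Statistical analyses names no covariate for the survival model.

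**Data at hand.** Recruitment says that the screening questionnaire has "items assessing parental smoking status". Table 1 lists parents' smoking, reported by the mother at baseline and by the child at every wave. Randomisation follows the baseline assessment.

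**The article's own view of parental smoking.** Background lists it among the predictors of smoking experimentation. The Asthma section states: "Smoking parents are less involved in anti-smoking socialization than non-smoking parents". It also states: "adolescents with asthma are more likely to have parents who smoke than adolescents without asthma".

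**The concern.** The effect that sizes the trial was observed in a different population, with materials that have since been altered. The modules aim to raise anti-smoking socialisation, and the article says smoking parents do less of it. Families of non-smoking mothers may therefore start closer to the target and gain less. If so, the average effect over all mothers would be smaller than 10 points, and a weak overall result could be read as a failure to replicate the U.S. trial.

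The group most like the U.S. families is inside this trial and identifiable from baseline data. An estimate for that group carries more weight if announced in advance than if produced after a disappointing overall result. The article does commit to one moderator, asthma, but not to the one that corresponds to its known departure from the source trial. Because children with asthma more often have smoking parents, an asthma-by-condition difference may also partly reflect parental smoking.

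**Working it through.** **1. The stated sample size.** Two proportions, 30% v 20%, two-sided 0.05, power 0.80:

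n = [1.960·√(2·0.25·0.75) + 0.842·√(0.30·0.70 + 0.20·0.80)]² / 0.10² = (1.200 + 0.512)² / 0.01 ≈ 293.2, so 294 per arm.

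The stated 428 implies an inflation of 428/294 = 1.456. This cannot be verified, because no intracluster correlation, cluster size or missing-data allowance is given. It is the only figure consistent with the article's own target: 428/1.456 = 294 effective children per arm gives 80% power at 10 points, whereas treating all 428 as independent would give 92%. Power below therefore uses effective numbers: 294 per arm for 428, and (1399/2)/1.456 = 480 per arm for the 1399 never smokers, assuming an equal split.

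**2. Effect in smoking-mother families.** Background reports 19% v 12% for the U.S. trial. The crude odds ratio is (0.19/0.81)/(0.12/0.88) = 1.72. From a 30% control rate, odds 0.4286/1.72 = 0.249 give 19.9%, a 10.1-point difference. So the 10 points agree with the crude U.S. odds ratio moved to a 30% base rate, although the article does not say that this is how they were reached.

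**3. Pooled difference.** Two inputs are assumptions, not in the documents: the share s of mothers who smoke (20-40%) and the effect in the rest. The control rate is 30% in both groups. Half the log-odds effect is an odds ratio of √1.72 = 1.31, which takes 30% to 24.6%, a 5.4-point difference.

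Pooled difference = s × 10.1 + (1 − s) × 5.4

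Power = Φ{[d − 1.960·√(2·p̄·(1−p̄)/n)] / √[(p₁(1−p₁) + p₂(1−p₂))/n]}, with n the effective number per arm.

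| Effect in non-smoking-mother families | s | Pooled difference (points) | Power, 428 per arm | Power, 1399 children |
|---|---|---|---|---|
| Half | 20% | 6.3 | 41% | 60% |
| Half | 30% | 6.8 | 46% | 66% |
| Half | 40% | 7.2 | 51% | 72% |
| None | 20-40% | 2.0-4.0 | 8-19% | 10-28% |
| Equal | any | 10.1 | 81% | 95% |

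**4. Power of the interaction test.** Take 10 points with smoking mothers, 0 in the rest, and 1399 children. For s = 20% the effective numbers per arm are 1399 × 0.2 / 2 / 1.456 = 96 and 384.

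SE = √(0.37/96.1 + 0.42/384.4) = 0.0703, and power = Φ(0.10/0.0703 − 1.96) = 29.5%.

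For s = 30% and 40%, power is 36.7% and 40.5%. The range is therefore about 30-41%, or 40-55% with no inflation at all. With 10 v 5 points it is only 11-14% (inflated).

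These calculations compare proportions at 36 months and stand in for the planned survival analysis. Applying the overall inflation within strata is approximate.

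**The case against.** **The data do allow the question to be answered.** A reader might infer that the trial cannot tell a failed replication from a diluted effect. The article does not support that. Parental smoking is collected before randomisation, further moderators are foreseen, and nothing rules out an analysis by maternal smoking. This objection stands; what remains is that the article makes no commitment to that analysis.

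**Moderator lists and covariates often sit in a fuller document.** This is true, and their absence alone would be no finding. But the article does state an effect size and its source, and that source is a different population. That choice can be reviewed as written, and the moderator point follows from it.

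**Dilution is assumed.** This stands. Less socialisation among smoking parents does not prove that non-smoking mothers gain less; smoking mothers might also use the modules less. Refocusing the modules may have dealt with the change of population. Neither the share of smoking mothers nor their relative effect is in the documents.

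**The moderator test would rarely settle the matter.** This also stands, given the power in step 4. A null result could equally come from the translated materials or the factsheet control. Low power is a reason to report stratum estimates with intervals rather than rely on the interaction p-value.

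**The asthma comparison makes no causal claim.** Agreed. The plan asks whether the effect differs for children with asthma, and adjusting for maternal smoking answers another question. A reader might infer that the asthma test is invalid; it is not. A joint model belongs in a sensitivity analysis.

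**Conclusion.** The point holds in a limited form. Hypothesis 1 and the 10-point effect come from a programme for smoking mothers and are applied to a mixed population with partly refocused modules, and no reason is given for expecting the same effect. Maternal smoking is the known population difference from the source trial, yet only asthma is named as a moderator.

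The size of any loss is conditional. With 20-40% smoking mothers and half the log-odds effect in the rest, power falls from the stated 80% to about 41-51% at 428 per arm. The over-enrolment to 1399 brings it back only to 60-72%. With an equal effect there is no loss, and 1399 children give about 95%. All of this rests on a 30% control rate in both groups and on the 1.46 inflation implied by 428, which the article does not break down. The documents do not establish that dilution will occur. The case for change is that it is cheap and uses a prognostic variable already collected.

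**What to change.** **Statistical analyses.**
- Include baseline maternal smoking as a covariate in the primary survival model. This assumes that the mother's own status can be taken from the baseline parental smoking items.
- Pre-specify maternal smoking by condition as a secondary moderator analysis beside asthma. Report the intervention effect with its confidence interval in each stratum. State that the interaction test has low power, about 30-41% even for 10 points v 0 with 20-40% smoking mothers assumed.
- Fit asthma and maternal-smoking interactions together only as a sensitivity analysis.

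**Sample Size Calculation.**
- State that the source effect comes from a programme for smoking mothers, and give a reason for carrying it over if there is one.
- Add power at a smaller effect, such as 6-7 points, with its assumptions and the inflation used.

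**Cost.** Changes of wording and extra model terms, with no new data. The downsides are one more pre-specified comparison and a less favourable power statement.

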### Data collection

An overview of all measurements is given in Table 1. All questions will be administered during a 20-minutes telephone interview by one of the trained interviewers. At baseline, mothers will be interviewed first to check the eligibility of the family. Children will be interviewed few days later. Because of practical reasons, the over-enrolled families will be asked to answer the questions by questionnaire which will be sent to their homes. Only the children will be examined at post-intervention and follow-ups. We considered collecting data from parents at each follow-up, but we opted not to because (a) such data are not needed to test the study hypotheses and (b) our perspective is that children's perceptions of anti-smoking socialization are more reliable (less biased) and will explain their smoking status better than parental reports of anti-smoking socialization (see also [38-40]).

**Table 1 T1:** Overview of measurements

Measurement	Baseline		Post-intervention (6 months after baseline)	Follow-up I (12 months after baseline)	Follow-up II (24 months after baseline)	Follow-up III (36 months after baseline)
	Mother	Child	Child	Child	Child	Child
Demographic characteristics	X					
Smoking behavior parents [57]	X	X	X	X	X	X
Smoking behavior child [57]	X	X	X	X	X	X
Anti smoking socialization:						
Communication about smoking [46]	X	X	X	X	X	X
Monitoring [19]	X		X	X	X	X
Availability of cigarettes at home [19]	X	X	X	X	X	X
Parental norms [19]	X		X	X	X	X
Parental influence on their offspring smoking [19]	X	X	X	X	X	X
House rules [19]	X	X	X	X	X	X
Constructive reaction: perceptions of the parents reaction [19]		X	X	X	X	X
Intention to smoke [58]		X	X	X	X	X
Self-efficacy [49,59]		X	X	X	X	X
Attitude [60]		X	X	X	X	X
Social Norm [61]		X	X	X	X	X
General Parenting Style	X	X	X	X	X	X
Smoking behavior peers [62]		X	X	X	X	X
Parent-child relationship (NRI) [63]	X	X	X	X	X	X
Alcohol use		X		X	X	X
Strength and Difficulty Questionnaire (SDQ) [51]	X	X		X	X	X
Asthmatic symptoms (ISAAC) [50]	X	X		X	X	X
Program Evaluation/utilization [20]			X			

During the intervention program, 10% of the participants in the intervention condition will receive a telephone call from a trained interviewer about the procedure of the program. They will be asked if they received the activity modules and which modules they did utilize so far. The answers will give us an indication about program exposure among intervention condition families.

The post-intervention measurement (after 6 months) will collect more detailed information on program utilization. The three follow-up measurements will be at 12, 24, and 36 months after baseline. We have decided to follow the children for 36 months, indicating that at the final wave, children will be 12 to 14 years old. The national prevalence data on smoking in adolescents have shown an increase in ever smoking of 5% among 10-year olds, 7% among 11-year olds, 17% among 12-year olds, and of 25% among 13-year olds [2].

